### Blinding

Participants will be informed at the onset that they will be randomly assigned to 1 of 2 web-based interventions, with the design making it challenging for them to discern their assigned intervention. This ensures participants are blinded to their group allocation throughout the intervention, postintervention surveys, and interviews. The comparative group will only be unblinded after completing the interview phase, at which point they will be offered the intervention provided to the experimental group. Research assistant B will be temporarily hired solely for participant allocation, and the other researchers, including research assistant A, will not participate in the allocation process.

### Data Collection Methods

#### Survey Data

Outcomes and demographic and pregnancy- and birth-related characteristics data collection will be managed on the web by research assistant A, using survey URLs sent to participants. To ensure comprehensive data collection, during the posttest phases T1 and T2, participants will receive reminder SMS text messages on the first, third, and sixth days (for nonrespondents), prompting completion of the survey. Additionally, use data will be systematically gathered from the web program’s administrative interface. These data will be requested at regular intervals throughout the study to ensure comprehensive coverage and accuracy in our analysis of participant engagement.

#### Interview Data

To enrich the quantitative findings and delve into barriers to intervention participation, qualitative interviews will be conducted with 30 participants, selected purposefully to represent diverse experiences across both experimental and comparison groups and varying outcomes. These semistructured interviews will be carried out by the research team via Zoom (Zoom Video Communications, Inc) or KakaoTalk, aiming for an insightful blend of video and voice meetings. Immediate transcription will follow each recorded interview, with data analysis facilitated by NVivo software (version 14 for Windows; Lumivero). Prior to interviews, investigators will familiarize themselves with participants’ demographic, baseline, and both T1 and T2 data. Training for interviewers will emphasize techniques for fostering a comfortable atmosphere, building rapport, maintaining neutrality, and eliciting detailed responses. The research team will hold weekly debriefing sessions to discuss any new findings or issues encountered during data collection.

### Data Management

To safeguard participant confidentiality, unique identification numbers will anonymize all data, which will be encrypted and stored in a nonidentifiable format. These data, alongside automatically generated identification codes, will be kept on a dedicated USB storage device and secured in locked filing cabinets, accessible solely to the designated data analyst. In line with Daegu Catholic University’s research data management policy, all data will be retained by the principal researcher ([name]) for 3 years after study completion. Subsequent to this period, all documents will be destroyed, and digital files permanently erased to ensure irretrievability.

### Data Analysis

#### Quantitative Data Analysis

The quantitative data collected will be processed using SPSS Statistics (version 25.0; IBM Corp). Descriptive statistics, including frequency, percentage, mean, and SD, will evaluate demographic and pregnancy- and birth-related characteristics. The analysis of primary, secondary, and feasibility outcomes will also include mean, SD, and tests for normal distribution. To compare the homogeneity of characteristics and outcomes (T0) between experimental and comparative groups, chi-square tests and 2-tailed *t* tests will be applied. Depending on the homogeneity of baseline characteristics and initial SMSE-PBP scores, either repeated measures ANOVA or repeated measures analysis of covariance will be used. For nonnormally distributed data, generalized estimating equations will be used. Subgroup analyses based on demographic and pregnancy- and birth-related characteristics (eg, age and education level) will be conducted using linear or logistic regression. The use of the web-based intervention (the number of logins during the intervention period, the number of series completed to the end, and the number of endings collected for each series) in the experimental group will be assessed for primary, secondary, and feasibility outcomes using linear regression analysis. The reliability of measurement tools will be assessed using Cronbach α coefficient, and missing data will be addressed through multiple imputation.

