**Methods:**

Using an explanatory sequential mixed methods design, this study first conducts a quantitative analysis followed by a qualitative inquiry to evaluate outcomes and feasibility. Participants are randomly assigned to 2 groups: one accessing the PSIDK-iWebtoons and the other receiving Pregnancy Story I Didn’t Know in Text-Based Information (PSIDK-Texts) over 3 weeks. We measure primary efficacy through the self-management self-efficacy scale for premature birth prevention (PBP), alongside secondary outcomes including perceptions of susceptibility, severity, benefits, and barriers based on the health belief model for PBP and PBP intention. Additional participant-reported outcomes are assessed at baseline, the postintervention time point, and the 4-week follow-up. The feasibility of the intervention is assessed after the end of the 3-week intervention period. Outcome analysis uses repeated measures ANOVA for quantitative data, while qualitative data are explored through content analysis of interviews with 30 participants.

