### Sample Size

The sample size was calculated using G*Power software (Heinrich Heine University) [30], considering the absence of identical measurement tools and programs for an independent *t* test. A medium effect size of 0.50, a 1-sided significance level of 0.025, a power of 0.80, and an equal allocation ratio (1:1) for the 2 groups were assumed. This analysis determined that a total of 128 participants are required. Given the dropout rates of 20%-40% reported in previous web education program research [31,32], we anticipate a 30% dropout rate. To accommodate this, the study aims to enroll a total of 182 participants, allocating 91 participants to both the experimental and comparative groups, respectively.

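### Baseline significance tests and a normality check choose the primary model, so it is not fixed in advance and adjustment for the baseline SMSE-PBP score is not guaranteed

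*Protocol article*

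**What the plan says.** The Protocol article, Quantitative Data Analysis, first plans significance tests of baseline differences: "To compare the homogeneity of characteristics and outcomes (T0) between experimental and comparative groups, chi-square tests and 2-tailed" t tests. It then makes the main model conditional on baseline balance: "Depending on the homogeneity of baseline characteristics and initial SMSE-PBP scores, either repeated measures ANOVA or repeated measures analysis of covariance will be used". Normality is tested as well: "The analysis of primary, secondary, and feasibility outcomes will also include mean, SD, and tests for normal distribution". A second switch follows: "For nonnormally distributed data, generalized estimating equations will be used".

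The section gives no threshold for homogeneity or for normality and no covariate list. It does not say whether the group effect or the group-by-time effect is the primary test.

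The Abstract (Methods) is unconditional: "Outcome analysis uses repeated measures ANOVA for quantitative data". It also says that outcomes are "assessed at baseline, the postintervention time point, and the 4-week follow-up", so T0 is one of three measurement times. Under Allocation, participants are randomised in blocks, stratified by childbirth experience.

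**The concern.** Apart from the stratification factor, which the design balances, any baseline difference between randomised arms is due to chance. A chi-square or t test of that difference tests a null hypothesis already known to be true. Using its result to select the primary model hands the selection to chance.

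Three things follow.

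- **The primary analysis cannot be identified beforehand.** Three models are possible: repeated measures ANOVA, repeated measures ANCOVA and GEE. The Abstract and the analysis section do not agree on the starting point.
- **The T0 SMSE-PBP score is not assured as a covariate.** It is not one in the ANOVA branch. In the ANCOVA branch the plan does not say that it is one either: if the switch were triggered by, say, income, the covariate might be income alone.
- **Imbalance that is real but not significant is not corrected by regression on T0.** The estimate in that trial is then shifted up or down.

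This is a rule that the article states, not a detail left to an analysis plan. An analysis plan that fixed one model would contradict it.

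**Working it through.** **1. The plan's own figure.** Inputs from Sample Size: d = 0.50, one-sided 0.025, power 0.80, 1:1 allocation. The exact noncentral t calculation gives power 0.795 with 63 per arm and 0.8015 with 64 per arm, so 128 in total is reproduced. Inflation for 30% dropout: 128/0.7 = 182.9, against 182 stated; the difference is immaterial. The checks below use 64 per arm.

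**2. How often the baseline gate fires by chance.** The demographic and pregnancy-related section lists 6 + 7 = 13 characteristics (high-risk factors counted once). With the SMSE-PBP score that makes 14.
- Only the score tested at 0.05: 5% of trials.
- All 14 tested independently at 0.05, any one hit switching the model: 1 − 0.95^14 = 0.512.
- 13 tests, leaving out childbirth experience as the stratification factor: 1 − 0.95^13 = 0.487.

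The article does not say which of these gates applies.

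**3. Power, one follow-up time.** Let ρ be the T0-to-follow-up correlation (not given; 0.3, 0.5 and 0.7 assumed) and take SD = 1. The variance factor is 2(1 − ρ) for a change contrast and 1 − ρ² for ANCOVA. Power = Φ(0.5/√(factor × 2/64) − 1.96).

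| ρ | Change: factor | Change: power | ANCOVA: factor | ANCOVA: power |
|---|---|---|---|---|
| 0.3 | 1.40 | 0.67 | 0.91 | 0.84 |
| 0.5 | 1.00 | 0.81 | 0.75 | 0.90 |
| 0.7 | 0.60 | 0.95 | 0.51 | 0.98 |

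Simulating the rule (gate on the T0 score only at p<0.05, change contrast if it does not fire, ANCOVA if it does) gives about 68, 81 and 96%. Always using ANCOVA gives 83–85, 89–90 and about 98%. The ranges cover independent simulations.

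**4. Power, T1 and T2 averaged** (20,000 simulated trials per setting, compound symmetry, same gate).

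| ρ | Rule, group-by-time test | Rule, group effect over T0/T1/T2 | Always ANCOVA |
|---|---|---|---|
| 0.3 | 0.702 | 0.748 | 0.962 |
| 0.5 | 0.850 | 0.658 | 0.977 |
| 0.7 | 0.975 | 0.572 | 0.996 |

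The direction is the same. The size depends on which ANOVA effect counts as primary.

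**5. Type I error.** In the step 4 simulations with no true effect, the rule rejects in 4.3–4.6% of trials (group-by-time) or 2.4–3.3% (group effect). Always ANCOVA rejects in 5.0–5.2%.

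**6. Non-significant imbalance, ρ = 0.5.** Take a baseline difference of about 0.26 SD, inside the non-significant range 0.20–0.34. The expected change contrast is 0.50 + 0.5 × 0.26 − 0.26 = 0.37 if baseline favours the webtoon arm, and 0.50 − 0.13 + 0.26 = 0.63 if it favours the text arm. The critical value is about 1.98 × √(2/64) = 0.35. Given the baseline difference, the standard error is √(0.75 × 2/64) = 0.153. Power is therefore Φ((0.37 − 0.35)/0.153) ≈ 55% one way and Φ((0.63 − 0.35)/0.153) ≈ 97% the other. Simulations gave 54–56% and 96–97%. ANCOVA stays near 90% both ways, with its estimate centred on 0.50. Each direction occurs in about 10% of trials.

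**The case against.** The case for leaving the rule alone has real content.

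- **No false-positive problem.** A reader might infer that choosing a model from the data inflates type I error. Step 5 shows that overall it does not; the rule is mildly conservative. This stands.
- **The score is not left out when it would help most.** That reading is tempting but wrong. With T1 and T2 averaged and ρ = 0.5, ANCOVA gains 0.978 − 0.844 = 0.13 over the group-by-time test when baseline is not significantly different, and 0.967 − 0.668 = 0.30 when it is. The second case is where the plan may adjust. T0 is also probably a level of the time factor in the ANOVA, so it is missing as a covariate rather than discarded.
- **Chance does not demonstrably pick the estimand.** Under randomisation, a change contrast and a T0-adjusted contrast at the same time point estimate the same mean difference, and an identity-link GEE would keep it. The target would change if the ANOVA group effect were primary: a true effect of 0.50 at T1 and T2 averages (0 + 0.50 + 0.50)/3 = 0.33 over three times. It would also change if the two-degree-of-freedom interaction were primary. The article names no contrast, so neither reading can be asserted.
- **The one-in-two switch and the power loss must not be combined.** They assume different gates. If the switch fired in 51% of trials and always brought in T0, power would be about 0.488 × 0.807 + 0.512 × 0.904 = 0.86 at ρ = 0.5, and 0.488 × 0.667 + 0.512 × 0.843 = 0.76 at ρ = 0.3. Independence is also doubtful, since childbirth experience and number of children are related.
- **The conditional bias is symmetric.** It averages to zero over randomisations, and the low-power case has an equally likely mirror image.
- **The planned power is often still met.** In step 3 the rule reaches 81% at ρ = 0.5 and 96% at 0.7, and falls below 80% only at 0.3.

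These points limit the size of the problem. They do not supply a reason to let tests of a known-true null choose the primary model.

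**Conclusion.** The concern holds in a limited form. The article states a data-dependent rule for the primary analysis, and its Abstract and analysis section differ. The T0 SMSE-PBP score is not guaranteed as a covariate. Against always adjusting, the loss in the one-follow-up setting is about 15 to 17 percentage points of power at a correlation of 0.3, 8 to 9 at 0.5 and about 2 at 0.7. In any one trial, a non-significant baseline imbalance also shifts the estimate, in either direction.

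These figures rest on 64 evaluable women per arm, d = 0.5, normal data, a change-type contrast, and a gate on the T0 score alone at p<0.05. The gate level and the correlations are not in the article. That a switch could occur in about half of trials is a separate scenario (14 independent tests, any hit counts).

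The article does not support a claim of inflated type I error, or a firm claim that the estimand changes between branches. The sample size reproduces and is not affected. Severity: should be fixed, because the remedy uses data already collected.

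**What to change.** Delete both switches and state one model. For SMSE-PBP, and for each secondary score measured at T0, use one prespecified repeated measures ANCOVA or linear mixed model on T1 and T2. Include arm, time and arm-by-time, and always include the T0 value of that score and childbirth experience (the stratification factor). Either model cures the defect; the choice between them is secondary.

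- Name the primary contrast and time point, and report the adjusted arm difference with its 95% confidence interval.
- Present baseline characteristics descriptively, without significance tests.
- Keep GEE, or robust or bootstrap intervals, as a sensitivity analysis that does not replace the primary model.
- Make the Abstract and the analysis section state the same model.

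The cost is wording only; no further data are needed. Trial Status reports that quantitative data collection ended in March 2024, with analysis to finish by October 2024. The chosen model should therefore be documented and dated before the arms are compared. If they have already been compared, the report should say so.

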### Objectives

This study is designed to evaluate the efficacy and feasibility of “Pregnancy Story I Didn’t Know in Interactive Webtoon Series (PSIDK-iWebtoons),” an interactive web program aimed at preventing premature birth. The efficacy of the intervention will be assessed by comparing self-reported self-management self-efficacy for premature birth prevention (SMSE-PBP), health belief model scale for premature birth prevention (HBM-PBP), and premature birth prevention intention (PBPI) among WCA who receive the PSIDK-iWebtoons intervention to those who receive the text-based version, “Pregnancy Story I Didn’t Know in Text-based Information (PSIDK-Texts).” To explore the feasibility of PSIDK-iWebtoons, we will examine participants’ satisfaction using the Client Satisfaction Questionnaire-8 (CSQ-8) and evaluate the quality of the website, comparing responses between the 2 groups. Additionally, insights into the intervention’s effects and feasibility will be further drawn from a qualitative content analysis based on interviews with participants conducted after the second postintervention period (T2) and from usage data of the intervention recorded through web activity tracking.

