#### Secondary Outcomes

##### Health Belief Model Scale for Premature Birth Prevention

This scale assesses perceived susceptibility, severity, benefits, and barriers regarding premature birth, featuring 4 dimensions across 15 subscales with 96 items, validated for reliability [26]. The number of items in the 4 dimensions of the HBM-PBP is as follows: perceived susceptibility (21 items), severity (26 items), benefits (27 items), and barriers (22 items).

Each item on this scale is rated using a 5-point Likert scale that ranges from 1=not likely at all to 5=very likely. The scores for each dimension are computed as the mean of the total item scores, ranging from 1 to 5. Higher scores across these dimensions indicate stronger health beliefs and perceptions concerning the susceptibility, severity, benefits, and barriers of premature birth. At the time these measures were developed, the Cronbach α values were established as 0.87 for perceived susceptibility, 0.94 for perceived severity, 0.94 for perceived benefits, and 0.92 for perceived barriers [26].

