##### Premature Birth Prevention Intention

The PBPI score assesses participants’ intentions toward preventing premature birth. This instrument was specifically developed for this trial, drawing upon previous research on prevention intention. Participants respond to 3 statements: “I intend to do something to prevent premature birth,” “I plan to do something to prevent premature birth,” and “I will try to do something to prevent premature birth.” Responses are captured on a 7-point Likert scale from 7=strongly agree to 1=strongly disagree. The mean of the total item scores, ranging from 1 to 7, reflects the intensity of the participant’s prevention intention, with higher scores indicating stronger intentions toward preventing premature birth.

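### The rule for choosing between repeated measures ANOVA and ANCOVA uses no outcome baseline except SMSE-PBP and provides no own-baseline adjustment for the four HBM-PBP dimensions or PBPI, which costs precision on secondary outcomes

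*Protocol article*

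**What the plan says.** In the Protocol article, Quantitative Data Analysis first orders baseline comparisons: "To compare the homogeneity of characteristics and outcomes (T0) between experimental and comparative groups, chi-square tests and 2-tailed *t* tests will be applied". These cover every outcome at T0. The model is then chosen by one rule: "Depending on the homogeneity of baseline characteristics and initial SMSE-PBP scores, either repeated measures ANOVA or repeated measures analysis of covariance will be used". The rule has two triggers, baseline characteristics and the initial score of the primary outcome. It lists no covariates, and the section gives no separate model rule for the secondary outcomes.

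The Objectives treat the secondary scales as efficacy outcomes: "The efficacy of the intervention will be assessed by comparing self-reported" scores on SMSE-PBP, HBM-PBP and PBPI between the arms. HBM-PBP yields four scores (susceptibility, severity, benefits, barriers): "The scores for each dimension are computed as the mean of the total item scores, ranging from 1 to 5". PBPI adds a fifth, a three-item mean from 1 to 7. On timing, the abstract says: "Additional participant-reported outcomes are assessed at baseline, the postintervention time point, and the 4-week follow-up". On the model it says only: "Outcome analysis uses repeated measures ANOVA for quantitative data". Nowhere is it stated whether T0 is a level of the time factor. The Allocation section stratifies on childbirth experience alone, so no T0 score is balanced by design.

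**The concern.** The T0 scores of the five secondary outcomes are collected and tested for balance, but the model rule makes no use of the result. Followed as written, the choice of model for an HBM-PBP dimension or PBPI turns on participant characteristics and on the baseline of a different scale.

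Two things are at stake, both for secondary efficacy results only. The first is precision: a change-type comparison is noisier than one adjusted for the score's own baseline. The second is interpretation when the arms happen to differ at T0. A change-type estimate then moves in the opposite direction to the imbalance (regression to the mean), so part of an apparent effect, or of its absence, can reflect that imbalance.

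This is separate from how the primary model is chosen. Fixing ANCOVA on SMSE-PBP in advance would still leave the other five scores without their own baseline.

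**Working it through.** **Inputs from the Protocol article.** Sample Size: d = 0.50, one-sided 0.025, power 0.80, 1:1, 128 required, 30% dropout, 182 enrolled (91 per arm). Five secondary scores. **Assumed, because not given:** the correlation r between a score at T0 and at follow-up, taken as 0.3 to 0.8, with equal SDs at each time.

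**The plan's own figure.** Noncentral t with d = 0.50 and one-sided 0.025 gives 64 per arm, total 128, power 0.80. It reproduces. It rests on an unadjusted t test, so this point does not touch it.

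**Precision.** Take one follow-up and an SD of 1. The variance of the group contrast is proportional to 2(1 − r) for change from T0 and to 1 − r² for ANCOVA on own T0. The ratio is (1 − r²) / [2(1 − r)] = (1 + r)/2. Power below is for d = 0.50 with 64 per arm, two-sided 0.05, noncentral t. The d is borrowed from the primary outcome for illustration.

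| r | change | own-T0 ANCOVA | ratio | variance saved | power, change | power, ANCOVA |
|---|---|---|---|---|---|---|
| 0.3 | 1.40 | 0.91 | 0.65 | 35% | 0.66 | 0.84 |
| 0.5 | 1.00 | 0.75 | 0.75 | 25% | 0.80 | 0.90 |
| 0.7 | 0.60 | 0.51 | 0.85 | 15% | 0.95 | 0.98 |
| 0.8 | 0.40 | 0.36 | 0.90 | 10% | 0.99 | 0.997 |

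**Would adjusting for SMSE-PBP help instead?** Assume SMSE-PBP at T0 correlates 0.3 with the secondary T0 score, and with its follow-up only through that score. Its covariance with change is then −0.3(1 − r). The share of change variance explained is 0.09(1 − r)² / [2(1 − r)] = 0.045(1 − r): about 3% at r = 0.3 and 1% at r = 0.7.

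**Effect of a chance imbalance.** If the arms differ by δ at T0 with no treatment effect, the expected follow-up difference is rδ. The expected change difference is rδ − δ = −(1 − r)δ. At δ = 0.35 SD this is −0.25, −0.18, −0.11 and −0.07 SD for r = 0.3, 0.5, 0.7 and 0.8. Under own-T0 ANCOVA it is 0.

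**How likely is such an imbalance?** The SE of a T0 difference is √(2/n).
- All 91 per arm: √(2/91) = 0.148; 0.35/0.148 = 2.36; two-sided probability 0.018; over five independent scores 1 − 0.982⁵ ≈ 0.09.
- 64 completers per arm: √(2/64) = 0.177; 0.35 SD is almost exactly the 5% threshold (1.96 × 0.177 = 0.346); over five independent scores 1 − 0.95⁵ = 0.226 at that threshold (0.217 at exactly 0.35).

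Positive correlation between the scores lowers both figures.

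**Simulation** (8,000 trials per setting, 64 per arm, T0/T1/T2 with equal correlation r = 0.5, no effect). Overall rejection was 0.053 for group × time and 0.046 for own-T0 ANCOVA of the T1/T2 mean, so type I error is controlled either way. Among the 5% of trials with a significant T0 difference, rejection was 0.18 for group × time and 0.05 for ANCOVA.

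**The case against.** The strongest reply is that the section lists no covariates for any outcome. The rule could be meant for SMSE-PBP alone, with secondary covariates left to a fuller document, as is common for a condensed article. This stands in part. A reader might infer that HBM-PBP and PBPI are never adjusted for their own T0 scores; the text does not say so, only that no such adjustment is provided. A reader might also infer that SMSE-PBP is the sole trigger, but baseline characteristics are named in the same sentence. What remains is more than missing detail: the article does fix a model rule, and the only outcome baseline it names belongs to another scale.

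A second reply is that repeated measures ANOVA with T0 as a time level already uses each score's own T0. That is right, and a reader who infers that imbalance goes uncorrected would be wrong. The group × time contrast subtracts T0 in full, which is too much rather than too little. Nor is the test invalid, since overall type I error holds under randomisation.

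A third reply concerns size. HBM-PBP dimensions have 21 to 27 items and reported α of 0.87 to 0.94, so r may be high and the gain near 10%, with little change in power. Multiple imputation is planned, so all 91 per arm can contribute T0 data, which favours the 9% figure. Both points are fair. They apply less to PBPI, a three-item scale made for this trial with no reliability reported in the article, where a lower r is plausible.

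**Conclusion.** The point holds as a correctable weakness in the secondary analyses. The rule provides no own-T0 adjustment for five efficacy scores whose baselines are already measured. If the unadjusted repeated measures ANOVA is used with T0 as a time level, ANCOVA would remove 10% (r = 0.8) to 35% (r = 0.3) of the variance of the contrast. A chance T0 difference would be over-corrected by (1 − r) times its size.

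The conclusion rests on an assumed r, on T0 being a level of time, and, for the imbalance probabilities, on independence, which makes them upper figures. The finding that SMSE-PBP is a poor substitute covariate also rests on an assumed correlation of 0.3. Neither general bias nor an inflated type I error follows. The primary analysis and the sample size are outside this point.

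**What to change.** In Quantitative Data Analysis, state that each HBM-PBP dimension and PBPI is analysed at T1 and T2 with its own T0 score as covariate, whatever the baseline homogeneity tests show. In this form T0 is a covariate and not also a repeated outcome level. A longitudinal model that keeps T0 as a response but constrains the baseline means to be equal across arms is an acceptable equivalent.

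The cost is one sentence and one covariate per model. The T0 scores are already collected, so no further data or participants are needed.
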